## Abstract

A shallow sulcus characterizes trochlear dysplasia (TD) of the femoral trochlea, which can lead to chronic pain or instability of the patellofemoral joint. Breech presentation at birth has been identified as a risk factor for developing this condition, which an ultrasound can identify early. Early treatment could be considered at this stage, given the potential for remodelling in these skeletally immature patients. Newborns with breech presentation at birth who meet the inclusion criteria will be enrolled and randomised in equal proportions between treatment with the Pavlik harness and observation. The primary objective is to determine the difference in the means of the sulcus angle between the two treatment arms at two months. Ours is the first study protocol to evaluate an early non-invasive treatment for TD in the newborn with breech presentation at birth using a Pavlik harness. We hypothesised that trochlear dysplasia could be reverted when identified and treated early in life with a simple harness, as it is done with developmental dysplasia of the hip.

## 1. Introduction

The femoral trochlea consists of a groove or sulcus through which the patella slides during motion. This groove is the main stabilizer of the patellofemoral joint above 30° of knee flexion. Below 30°, the main stabilizer is the medial patellofemoral ligament (MPFL). The abnormal morphology of the trochlear groove characterizes trochlear dysplasia (TD). This groove has a physiologic concavity with a normal angle of 135 ± 10° [1,2]. If the morphology of the trochlear groove becomes flatter or convex, as is characteristic of TD, the patella is not properly stabilized during knee flexion.

TD is one of the most important contributors to patellar instability [3], presenting in 96% of patients with a history of patellar dislocation [4]. TD begins manifesting in adolescence and early adulthood. This condition has also been associated with anterior knee pain with or without maltracking [5] and instability [1]. These abnormal biomechanics might, in addition, lead to degenerative cartilage changes and patellofemoral osteoarthritis [6,7,8]. Considering this entity’s repercussions, it seems reasonable to apply a corrective treatment in more severe cases to treat recurrent dislocation episodes and prevent future patellofemoral degenerative complications. The mainstay treatment for instability with trochlear dysplasia type B and D of Dejour classification [9] is trochleoplasty, which can be associated with other additional gestures such as MPFL reconstruction and tibial tubercle transfers, among others. In childhood, trochleoplasty is not free of controversy. If necessary, a deepening trochleoplasty can be indicated in patients with high-grade trochlear dysplasia, with an expected growth of fewer than two years. This procedure has ultimately been shown to be able to reshape the trochlea in the skeletally immature patient [10,11,12,13]. However, this potential is limited in children older than ten years, and the procedure is technically demanding and not exempt from several potential complications [14]. Therefore, no current treatment allows trochlear remodelling to occur during this period, and this condition’s late manifestation makes an early diagnosis during childhood unlikely.

The aetiology of TD remains unclear. The articular surface of the sulcus is developed at birth. The osseous sulcus angle is inversely related to age, being flattest in the youngest children and deepening steadily through growth. By contrast, the cartilaginous sulcus angle stays virtually constant from birth to adolescence [15,16].

Some authors argue for the genetic origin of trochlear dysplasia [17,18], as the morphology of the distal femur seems to be the same in the foetus and the adult. Moreover, in congenital patellar dislocation, the sulcus is altered [19,20,21]. Another hypothesis contemplates that biomechanical factors could influence the final shape of the trochlear groove. Recurrent episodes of patellar dislocation in skeletally immature patients have been shown to lead to the development of TD in those without previous congenital abnormalities [8,10,11,22,23]. Additionally, experimental models on rabbits [10,11,23,24] have shown that an inadequate patellar position predisposes the distal femoral groove to become more flattened. This abnormal patellar position could modify the mechanical stress distribution, altering cartilage growth in immature skeletons or affecting its metabolism when mature, resulting in cartilage damage and early-onset osteoarthritis [6].

According to Frost’s theoretical cartilage growth force response curve [25], mechanical load partially regulates chondral growth. Decreased compression limits articular chondral growth because cartilage growth directly relates to compression until excessive forces beyond physiologic loads are reached that first retard and then stop growing. Therefore, when a foetus is in the breech presentation, an abnormal interaction between the patella and the trochlea could result in an intrauterine remodelling of a previously normal foetal knee.

The breech presentation is associated with TD [26,27,28], with a higher incidence in the frank breech position [28] where both legs are in extension. TD has also been related to patella alta [24,29]. Footling and frank breech positions could act similarly, resulting in a higher, more proximal patellar position, preventing it from engaging with the femoral trochlea. The decreased contact pressures result in diminished compression between the surfaces, and chondral tissue growth decreases, resulting in an abnormal trochlear groove depth.

During growth, cartilage is replaced with bone. Therefore, chondral remodelling could correct a deformity in skeletally immature patients [25]. To correct this condition, normal load distribution would need to be re-established. The patella enters the trochlear groove at the beginning of knee flexion, at approximately 30°, and the contact surface increases until it reaches its maximum at 90° [10]. Therefore, if the knee is maintained in this position for a period that allows remodelling, it would allow the maximum peak of physiologic compression to be exerted, stimulating cartilage growth and remodelling. For this purpose, the Pavlik harness could be used.

The Pavlik harness is widely used to treat developmental dysplasia of the hip (DDH) with a time-dependent correction success rate. However, the maximum period for treatment with the Pavlik harness has yet to be established [30]. Usually, the recommended period is a maximum of eight weeks for non-displaced hips [31]. Even though the hip and knee are different articulations, Frost’s cartilage growth principle [25] could similarly be applied. Since this is the first study to employ the Pavlik harness in TD, the ideal treatment period for this condition is unknown. Therefore, we will apply the eight weeks timeline for the treatment of TD with the Pavlik harness.

If TD could be early reverted with a simple harness in the newborn, as it is nowadays done with DDH, this could potentially normalize the patellofemoral joint biomechanics, increasing stability, enabling proper function, and preventing pain and early-onset degenerative arthropathy. Observation is the usual treatment for the first episode of dislocation in the pediatric patient. Patellofemoral instability often responds poorly to conservative treatment, and dislocation repeatedly recurs in a significant number of patients with risk factors for dislocation [32]. TD can be aggravated in patients with an immature skeleton experiencing recurrent episodes of dislocation, ultimately leading to an increase in instability, risk of cartilage deterioration, pain, and reduced health-related quality of life and financial costs [33]. MPFL reconstruction is usually the surgical technique of choice in paediatric patients. However, it does not avoid the risk of redislocation [34], especially when TD and other risk factors are present.

We therefore propose an early non-surgical and non-invasive treatment in newborns with an abnormal ultrasound femoral sulcus angle, applying a Pavlik harness for two months. We hypothesize that acquired factors in the development of the femoral trochlea are essential and that the femoral dysplastic trochlea can remodel early in life when appropriately identified and treated. We aim to provide a therapeutic option at the early stages of development to revert TD.

## 2. Materials and Methods

### 2.1. Methods: Participants, Interventions, Outcomes

The study is a registered clinical trial with ClincalTrials.gov ID: NCT05081453.

#### 2.1.1. Trial Design

The study is designed as a prospective, randomized, controlled, triple-blinded, superiority clinical trial with two parallel groups and a primary endpoint of trochlear dysplasia screening and treatment over two months. Randomization will be performed as block randomization with a 1:1 allocation.

#### 2.1.2. Study Setting

The present investigation will be conducted in the Orthopedic Surgery Department of Virgen de la Arrixaca University Hospital in Murcia (Spain), a level III Academic Hospital. For data and clinical outcomes, the Pediatric Radiology and Pediatric Orthopedic Surgery Departments will follow up with patients. The principal investigator and research assistant will perform data management and statistical coordination.

#### 2.1.3. Eligibility Criteria

Inclusion criteria:Healthy neonates;Breech presentation;Sulcus angle ≥ 159° in ultrasound;

Exclusion criteria:Older than three months of age;Cerebral palsy;Developmental dysplasia of the hip: pathological alpha angle according to Graf classification (except type IIa) in ultrasound, or clinical criteria: positive Barlow’s or Ortolani’s test, hip clicks, tightness of adductors, asymmetry of the skin folds;Developmental alterations;Chromosomopathies;Other pathologies that could be adversely affected by the introduction of the Pavlik harness.

#### 2.1.4. Interventions

Eligible patients will be randomized in equal proportions between treatment with the Pavlik harness and observation, as shown in Figure 1.

The pediatric orthopedic department will provide the harness in its commercially available form (ORLIMAN Pavlik Harness CE).

The harness will be placed with a hip flexion of 60° and a knee flexion of 90°, as shown in Figure 2. The Pavlik harness’s first placement will occur after clinical exploration by a pediatric orthopedic surgeon and an ultrasound exam. The pediatric radiologist performing the ultrasounds, the data collectors, and the data analysts will be blinded to the identity of the intervention group patients.

#### 2.1.5. Modifications

The patient will be monitored for concomitant pathologies that have arisen during treatment with the Pavlik harness to assess whether they will cause discomfort or difficulty for the patient and their family. In case of incompatibility, treatment with the Pavlik harness will be withdrawn.

#### 2.1.6. Adherence

A face-to-face evaluation of the subjects in the treatment group will be conducted after four weeks to assess the correct use of the harness.

It is beneficial to check daily the flexion creases of the knees, groin, and neck to identify possible chafing of the skin, in which case soft padding is applied to cover the straps.

During the first visit, the patient’s parents will learn recommendations for daily situations such as nappy changing, dressing, resting, breastfeeding, playing, and bathing at home. They will also receive a complete written guide. On the second visit, the researchers will interview the parents to learn about daily life adaptations such as breastfeeding, play, nappy changing, and dressing.

#### 2.1.7. Concomitant Care

Relevant concomitant care and interventions permitted or prohibited during the trial are detailed in the written guide provided to the treatment group patient’s caregivers. In this guide, they will also have a phone number to reach out in case questions need further clarification.

#### 2.1.8. Outcomes

Outcomes measures will be collected two months after the first visit.

Primary outcome measures:The difference in the means of the sulcus angle between the two treatment arms at two months.

Treatment success is defined as a sulcus angle < 159° visualized by ultrasound. A sulcus angle ≥ 159° is the value set to diagnose TD in our study population, and values < 159° are considered non-dysplastic.

For newborns, radiographs and CT are not optimal imaging modalities. Besides X-ray radiation, the patellofemoral joint is not ossified, so it is not visible [36]. MRI is not an optimal screening tool because of the need for sedation, limited availability, and costs. Ultrasound allows for the visualization of cartilage and bone and is a faster, cheaper, and more available technique, so it could be used as a screening tool for detecting TD [37]. An ultrasound sulcus angle > 159° is considered dysplastic in newborns [28].

In our study, the ultrasound will be performed by a single observer in all cases to eliminate any possible inter-observer variability.

Secondary outcome measures:The difference in the means of the sulcus angle at baseline and after two months for each group;The difference will be measured by comparing the mean sulcus angle before and after the two-month treatment for the intervention group and the baseline and after two months for the control group.

The difference between the two treatment arms will be measured by comparing the proportion of patients in each treatment group with dysplastic (≥159°) and non-dysplastic (<159°) sulcus angles.

#### 2.1.9. Participant Timeline

During the first four to six weeks of life, a bilateral knee ultrasound will be performed on neonates with a breech presentation to determine the sulcus angle. Then, they will be derived into the Pediatric Orthopedics and Traumatology Department, as stated in Figure 2.

Intervention group: The estimated duration of the Pavlik harness procedure is two months, with four-week revisions by a pediatric orthopedic surgeon. After two months, a pediatric radiologist will perform a second ultrasound to evaluate the sulcus angle, and the Pavlik harness will be removed. In both groups, a face-to-face consultation in pediatric orthopedic surgery will be performed at 6–9 months to assess the clinical progression, as shown in Figure 3.

Control group: the control group will be evaluated two months after the baseline ultrasound, with a second one performed by a pediatric radiologist, as shown in Figure 4.

#### 2.1.10. Sample Size

The study population are the newborns at TD of Virgen de la Arrixaca University Hospital. The total number of births in this institution in 2016 was 14,167. However, the frequency of TD in newborns is unknown.

Breech presentation is a risk factor for TD, and the frequency of breech presentation is between 3–5% [38]. We consider 5% to be the estimated frequency of this presentation at birth, which implies that approximately 708 newborns each year have a breech presentation in our population. TD (a pathologic sulcus angle) is identified in 10% of the breech presentation population [28]. Accordingly, we consider the number of newborns in our population with TD to be 71 per year.

For the ultrasound screening test, we need 116 ultrasounds to have a 95% confidence that the real value is within ±5% of the measured one. This estimation was calculated according to the following formula:$$n=\frac{\;\frac{Z_{\alpha }^{2}\cdot p\cdot \left(1-p\right)}{e^{2}}}{1+\left(\frac{Z_{\alpha }^{2}\cdot p\cdot \left(1-p\right)}{e^{2}\cdot N}\right)}$$
where *Z_α_* is the critical value of the normal distribution (for a confidence level of 95%, *α* is 0.05, and the critical value is 1.96), *e* is the margin of error (*e* = 5%), *p* is the sample proportion (*p* = 10%), and *N* is the population size (*N* = 708). Note that a finite population correction has been applied to the sample size formula.

For the estimation of the treatment groups sample size, the following formula is applied: $$n=\frac{2{\left(a+b\right)}^{2}\;\sigma^{2}}{{\left(\mu_{1}-\mu_{2}\right)}^{2}}$$
where *n* is the sample size in each group, a is the conventional multiplier for alpha, b is the conventional multiplier for power, σ is the sample variance, and *μ*_1_ − *μ*_2_ is the difference we aim to detect. The sample variance was calculated from a pilot study, from which we obtained a value of *σ* = 5.78.

To consider a difference of 10° in sulcus angles between the treatment and the control group as clinically significant (*μ*_1_ − *μ*_2_) and be detected with 80% power and a significance level alpha of 0.05, *n* = 5.25. That means six subjects per group is the minimum sample size.

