#### 2.3.3. Statistical Methods

The primary efficacy endpoint is the comparison of the treatment with the Pavlik harness for two months, measured by analyzing the initial ultrasound sulcus angle data and those obtained after the treatment period.

The Shapiro–Wilk test will be performed to assess the normality of data.

To determine if the Pavlik harness is more effective in reducing knee SA compared to no treatment, the results of the intervention group will be compared to the control group with the Student’s t-test for independent data. The intervention will be effective if it achieves statistical differences (with a 95% confidence) in the knee SA between the treatment and control groups before and after treatment.

To assess if the Pavlik harness is effective in reducing the knee SA within the treatment group, the Student’s t-test for dependent data will be applied to compare the values of the ultrasound sulcus angle at baseline and two months within each group (treatment and control).

A regression analysis will be performed to determine the relationship between the use of the Pavlik harness and knee SA while accounting for other factors that may affect the knee SA.

The difference in the proportion of participants between the two treatment arms who are classed as a treatment success at two months will be calculated with Fisher’s exact test of independence.

Missing data shall be treated using the multiple imputation procedure to identify patterns in the dataset’s missing data and replace missing values with plausible estimates.

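### Six infants per group gives 77% power, not 80%, with the planned two-sample t-test; 5.78 is also labelled a variance but used as a standard deviation

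*Protocol article*

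**What the plan says.** Section 2.1.10 of the protocol article sizes the treatment groups with n = 2(a + b)²σ²/(μ₁ − μ₂)², where a and b are the usual multipliers for alpha and power. The target is "a difference of 10° in sulcus angles between the treatment and the control group as clinically significant", to "be detected with 80% power and a significance level alpha of 0.05". The formula returns 5.25, which is rounded up: "That means six subjects per group is the minimum sample size".

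The only variability input is introduced with the words "σ is the sample variance", and then "The sample variance was calculated from a pilot study", "from which we obtained a value of *σ* = 5.78".

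Section 2.3.3 names the test for the between-arm comparison: the intervention group will be "compared to the control group with the Student’s t-test for independent data". The success rule is "The intervention will be effective if it achieves statistical differences (with a 95% confidence".

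**The concern.** The formula in 2.1.10 treats the standard deviation as known and uses normal critical values. That is a good approximation for large groups and a poor one for six per group, where the planned test must estimate the variance from 12 infants and uses a larger critical value. The formula therefore credits the design with more power than the planned test has.

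At stake is a design property that the plan states as fact, namely that six per group is enough for 80% power. If it is not, the plan should say so or name the number that is.

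The second matter is the label on 5.78. A variance and a standard deviation of the same numerical value imply very different trials, so a reader needs to know which one the pilot study produced.

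**Working it through.** **Inputs.** From 2.1.10: difference 10°, σ = 5.78, alpha 0.05, target power 80%, six per group. From 2.1.1: 1:1 allocation. From 2.3.3: Student's t-test for independent groups. I take one sulcus-angle value per infant, normally distributed with equal variance in the two arms.

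**Step 1: reproduce the plan's figure.** With a = 1.96, b = 0.8416 and 5.78 entered as a standard deviation:

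n = 2 × (1.96 + 0.8416)² × 5.78² / 10² = 2 × 7.849 × 33.41 / 100 = 5.24

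This agrees with the printed 5.25 apart from rounding, and it rounds up to 6.

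**Step 2: settle the two readings that the text leaves open.**

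- *Sidedness.* Section 2.1.10 does not state it for this formula. A one-sided alpha of 0.05 (a = 1.645) gives 2 × (1.645 + 0.8416)² × 33.41 / 100 = 4.13, which does not match. The plan's figure is therefore two-sided.
- *Variance or standard deviation.* If 5.78 were a variance, it would replace σ² and give 2 × 7.849 × 5.78 / 100 = 0.91 per group, which does not match either. The plan has used 5.78 as a standard deviation.

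**Step 3: power of the planned test.** With n per group, the t statistic has 2n − 2 degrees of freedom and noncentrality δ / (σ√(2/n)). At n = 6:

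- degrees of freedom = 10, two-sided critical value 2.228 (the formula uses 1.96)
- noncentrality = 10 / (5.78 × √(2/6)) = 10 / 3.337 = 2.997
- power from the noncentral t distribution = 77.0%

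A simulation of 400,000 trials of 6 + 6 infants also gave 77.0%. The normal approximation at n = 6 would give Φ(2.997 − 1.96) = 85.0%, so it overstates the power of the planned test by 8 points at this size.

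**Step 4: the number that reaches 80%.**

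| Per group | df | Power for 10° (SD 5.78, two-sided t-test) |
|---|---|---|
| 5 | 8 | 67.0% |
| 6 | 10 | 77.0% |
| 7 | 12 | 84.4% |

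The smallest equal allocation with at least 80% is seven per group, 14 in total. With six per group, 80% power is reached at a difference of about 10.4°.

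**Step 5: sensitivity to the pilot value.** The size of the pilot study is not given, so the uncertainty in 5.78 cannot be quantified from the article. For illustration, with assumed standard deviations:

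| Assumed SD | Power, 6 per group | Power, 7 per group |
|---|---|---|
| 5.5 | 81.0% | 87.7% |
| 5.78 (plan) | 77.0% | 84.4% |
| 6 | 74.0% | 81.6% |
| 6.5 | 67.1% | 75.3% |
| 7 | 60.8% | 69.0% |

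**The case against.** The best defence is that the plan's arithmetic is right for the formula it prints, and that the shortfall is small: three points of power, or one infant per group. Six is described as a minimum, so recruiting seven or more would contradict nothing. The type I error of the t-test at any fixed size is unaffected. Uncertainty in the pilot standard deviation moves power by more than the choice between normal and t critical values does. All of this stands, and it is why the point is a modest correction. It does not rescue the sentence itself: six is stated to be the minimum for 80%, and for the planned test it is not.

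Three stronger readings are tempting, and the article does not support them.

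- *A minimum with no fixed total invites stopping when the p-value is favourable.* No section plans a repeated look. Section 2.3.2 has the data evaluated once the study is finished, the Data Availability statement provides for a database lock, and sections 2.1.4, 2.2.1 and 2.2.2 blind the analysts to allocation. An inflated error rate would require testing that the article does not describe. A condensed article may also leave the final number to the full protocol.
- *The size ignores expected dropout.* The Discussion anticipates difficulty in persuading caregivers and in compliance with the harness, not missing two-month ultrasounds. An infant who wears the harness poorly but is scanned still contributes an outcome. Section 2.3.3 also provides multiple imputation, although that would not restore lost power. An attrition allowance is again a detail that an article may leave out.
- *The variance label undermines the sample size.* It does not, because the printed 5.25 is reached only with 5.78 as a standard deviation.

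**Conclusion.** The point holds as a modest correction. With the t-test named in 2.3.3, six infants per group has 77.0% power for 10°, three points below the stated 80%, and seven per group (84.4%) is the smallest equal allocation that reaches it. Calling 5.78 a variance is a wording error with no effect on n, provided the pilot study did yield 5.78 as a standard deviation.

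These figures rest on a two-sided alpha of 0.05 (implied by the plan's own 5.25 but not stated for that formula), a true standard deviation of 5.78, equal variances, normality, and one value per infant. The last is an assumption because the ultrasound is bilateral (2.1.9) and 2.3.3 refers to the angle of the knee without naming the unit of analysis.

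**What to change.** In 2.1.10, make one of two changes:

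- Keep six per group and state that it gives 77% power for a 10° difference (80% for about 10.4°) with the two-sided two-sample t-test at alpha 0.05.
- State seven per group as the minimum for 80% power, with an actual power of 84%.

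In either case, say that the calculation is two-sided and based on the t distribution, and call σ = 5.78 the standard deviation in both places where the text now says variance, after confirming it against the pilot data.

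The first option costs a restated sentence. The second costs two more infants in total, against the 71 newborns with trochlear dysplasia per year that the same section expects. Neither changes the analysis.
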